### Trial duration and follow-up assessment

The trial is planned to be initiated in summer 2015. The recruitment period of the entire study (100 patients) will take approximately 36 months. The primary endpoint of the study (acute toxicity) can be evaluated three months later. The follow-up period is three years. The whole study duration is estimated to be 75 months if the study is not terminated early (see criteria for termination). Follow-up visits are scheduled at 3 months after the end of treatment and 6-monthly thereafter, until the third year. Assessment includes overall survival, PSA-level, clinical recurrence-free survival with regard to local, regional and distant control. Time without treatment for prostate cancer and toxicity according to CTCAE 4.0 will be evaluated. QoL will be assessed at 3, 12, 24, 36 months after completion of treatment.

### Sample size calculation and criteria for termination of the study

The H0-hypothesis of the protocol is that ≥20 % of patients experience grade 3+ genitourinary and gastrointestinal acute toxicities (CTC v 4.0) or ≥30 % in case of pre-existing G2-toxicities.

Accordingly, the study is terminated if ≥20 % of patients (*n* = 10/50) experience grade 3+ genitourinary and gastrointestinal acute toxicities (CTC v 4.0) or ≥30 % in case of pre-existing G2-toxicities. If toxicity is below the mentioned threshold, the study will be continued to include 100 patients treated per protocol. In the final analysis (*n* = 100), the H0-hypothesis is rejected if ≤13 % (13/100) grade 3+ genitourinary and gastrointestinal acute toxicities (CTC v 4.0) were observed. This study (Simon’s design) has a significance level p < 0.05 and a power of 87.2 % if G3 + −toxicity is ≤10 %.

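### Ending enrolment at the 14th countable toxicity event in stage 2 would be a cheap improvement: from that point the final ≤13/100 rule cannot be met, yet the text directs enrolment on to 100

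*Protocol article*

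**What the plan says.** All the decision rules are in the protocol article, under the heading on sample size and termination criteria.

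- **Interim:** "the study is terminated if ≥20 % of patients (*n* = 10/50) experience grade 3"-or-higher events. A separate 30 % limit applies where grade 2 toxicity was already present.
- **After the interim:** "If toxicity is below the mentioned threshold, the study will be continued to include 100 patients"; the sentence goes on to specify that these are patients treated per protocol.
- **Final analysis:** "the H0-hypothesis is rejected if ≤13 % (13/100) grade 3+ genitourinary and gastrointestinal acute toxicities" were seen.
- **Operating characteristics:** "This study (Simon’s design) has a significance level p < 0.05" and "a power of 87.2 % if G3 + −toxicity is ≤10" %.

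The section on the rationale mentions a single interim safety analysis. The section on trial duration refers back to the same termination criteria. It gives recruitment of 100 patients in about 36 months, with the acute-toxicity endpoint evaluable three months later. The article states no boundary for patients 51 to 100.

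**The concern.** A trial that passes the interim does so with at most 9 events. From then on, the 14th event fixes the outcome: however the remaining patients fare, the final count cannot be 13 or fewer. Followed as written, the text still calls for enrolment to 100.

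The counted events are grade 3+ genitourinary and gastrointestinal toxicities, and the article itself says experience with salvage radio-thermotherapy is limited. Patients entered after the 14th event would receive the combination when the primary safety question can no longer be answered favourably.

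**Working it through.** **Inputs (sample size section).** Continue if X1 ≤ 9 of 50; reject H0 if X1 + X2 ≤ 13 of 100; null rate 0.20; target rate 0.10.

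**Step 1. Reproduce the stated figures.** With b(n, x, p) the binomial probability:

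P(reject) = Σ over x = 0..9 of b(50, x, p) × P(X2 ≤ 13 − x), with X2 ~ Bin(50, p).

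- p = 0.10: 0.8716, matching the stated 87.2 %.
- p = 0.20: 0.0459, below 0.05 as stated.

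**Step 2. Earliest decisive point.** With 9 events at patient 50, five more in succession put the 14th at patient 55, leaving 100 − 55 = 45 planned patients. This is the extreme case.

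**Step 3. How often, and how many patients remain.** Given x ≤ 9 at the interim, k = 14 − x further events are needed. The k-th falls at stage 2 patient m with probability C(m−1, k−1) p^k (1−p)^(m−k), leaving 50 − m patients. Summing over x and m:

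| True rate | Pass interim | Pass and reach 14th event | Mean patient of 14th event | Mean patients left when it occurs | Stage 2 saving averaged over all trials |
|---|---|---|---|---|---|
| 10 % | 0.976 | 0.104 | 89.9 | 10.1 | 1.05 |
| 15 % | 0.791 | 0.449 | 85.3 | 14.7 | 6.6 |
| 20 % | 0.444 | 0.398 | 79.4 | 20.6 | 8.2 |
| 25 % | 0.164 | 0.161 | 73.6 | 26.4 | 4.3 |

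At 20 %, 0.398 / 0.444 = 90 % of the trials that pass the interim reach a 14th event. Of the 20.6 patients then left, about 20.6 × 0.20 = 4 would have a grade 3+ event.

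**Step 4. Reporting lag.** The table assumes each event is known at once. Accrual is 100 / 36 = 2.78 patients per month. Three months of lag is 3 × 2.78 ≈ 8 patients. Adding the seven treatment weeks (7 / 4.345 = 1.6 months) gives 4.6 × 2.78 ≈ 13. Averaging max(0, patients left − lag) at 20 % gives about 13 patients with a lag of 8 and about 9 with a lag of 13. These lags are pessimistic, since a toxicity can be counted when it occurs and only its absence needs the full window.

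**Step 5. Effect of curtailment on alpha and power.** Every trial stopped at a 14th countable event would have finished with at least 14. No decision changes, so alpha stays 0.0459 and power 0.8716. Expected sample size falls from 72.2 to 64.0 at 20 %, and from 98.8 to 97.7 at 10 %.

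**Step 6. Would a running 20 % rule close the gap?** No. 14/70 = 20 %, but 14/71 = 19.7 %. A 14th event after patient 70 would not trigger it, and the average position at a true 20 % rate is patient 79.

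**The case against.** The strongest reply is that nothing here is wrong. A Simon two-stage design ordinarily has no curtailment in stage 2, and the stated power and significance level reproduce. That stands: this is an improvement, not a correction.

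Four stronger readings are tempting, and the document does not support them.

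- **That the plan exposes patients beyond its own safety limit.** The termination threshold is 20 %. A 14th event at patient 79 is 14/79 = 17.7 %, and a final 14/100 is 14 %. Failing to reject H0 means the rate was not shown to be below 20 %, not that the treatment was found unsafe.
- **That later patients add nothing.** They sharpen the toxicity rate and inform feasibility (set at 95 % of patients or more), quality of life, progression-free survival, time without ADT and the intended comparison with SAKK 09/10. However, the article makes phase III depend on the treatment being both safe and feasible, so these data weigh less once the safety criterion cannot be met.
- **That stage 1 must run to patient 50.** The wording can already be read as terminating at the tenth event. This matters for the size: at a true 30 % rate, stopping both stages early would save about 18 patients on average, but 16.9 come from stage 1 and only 1.2 from stage 2.
- **That there is no other safety monitoring.** The full protocol is not shown and may contain some. The point rests only on the termination criteria and the continuation instruction that the article does state.

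A flat event count is also not automatically neutral. The interim has a separate 30 % limit for pre-existing grade 2 toxicity, and the 100 are patients treated per protocol. A tenth or 14th event might therefore not count towards the stated limit.

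**Conclusion.** The point holds as a low-cost improvement. Once the interim is passed, the text directs enrolment to 100 even when 14 countable events have made rejection of H0 impossible. At a true rate of 20 %, about 40 % of all trials would be in that position, with about 20 planned patients left on average, or about 13 or 9 after allowing for 8 or 13 patients of lag. At the target rate of 10 % the average saving is about 1 patient, so a treatment that is as safe as hoped loses almost nothing.

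These figures assume independent patients with a common toxicity rate, the boundaries 9/50 and 13/100 applied to all patients, and steady accrual. They do not model the pre-existing grade 2 subgroup, because the article gives neither its size nor a final boundary for it.

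**What to change.** Add to the termination criteria that enrolment ends once the 14th primary-endpoint event that counts in the final ≤13/100 analysis is recorded. Clarify that the stage 1 check takes effect as soon as its own stated limit has been reached and later patients cannot reverse it. The same text must say how the 30 % limit for pre-existing grade 2 toxicity enters the count, and how events in patients outside the per-protocol-treated set are handled.

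This takes a short addition to the text and a running count of events. Alpha and power do not change provided that only events counted in the final rule trigger the stop. In trials that stop, the cost is a less precise toxicity rate and fewer patients for feasibility, quality of life, progression-free survival and the SAKK 09/10 comparison. If the sponsor prefers to complete enrolment for those purposes, the protocol should state that reason.

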### Primary endpoint

The primary endpoint is safety measured by frequency of grade 3+ genitourinary (GU) and gastrointestinal (GI) adverse events (AE) according to CTCAE version 4 [29]. Feasibility is defined as the number of hyperthermia treatments (*n* ≥ 7) and feasibility of radiotherapy according to protocol in ≥ 95 % of patients.

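### The final safety decision rests on 100 patients "treated per protocol", an undefined set that can leave out patients who stop because of the toxicity being measured

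*Protocol article*

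**What the plan says.** All references are to the protocol article.

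- **Sample size calculation and criteria for termination of the study.** The null hypothesis concerns patients in general: "The H0-hypothesis of the protocol is that ≥20 % of patients experience grade 3+ genitourinary and gastrointestinal acute toxicities". The interim rule does too: "the study is terminated if ≥20 % of patients (*n* = 10/50) experience grade 3" or higher events. For the second stage the wording narrows: "the study will be continued to include 100 patients treated per protocol". The final test follows directly: "the H0-hypothesis is rejected if ≤13 % (13/100) grade 3+ genitourinary and gastrointestinal acute toxicities". The design "has a significance level p < 0.05 and a power of 87.2" % at a true rate of 10 %.
- **Primary endpoint.** Safety is the frequency of grade 3+ GU and GI events, with no analysis set named. Feasibility requires at least seven hyperthermia sessions and "feasibility of radiotherapy according to protocol in ≥ 95 % of patients".
- **Trial duration and follow-up assessment.** "The recruitment period of the entire study (100 patients) will take approximately 36 months". Acute toxicity can be evaluated three months after that.

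The article does not define treatment per protocol. It has no rule on replacing patients, and it does not say that every treated patient counts for safety.

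**The concern.** The only population named for the final safety decision is a per-protocol one, and it is named in the sentence just before the test. For a toxicity endpoint that is a poor choice. Stopping radiotherapy early or missing hyperthermia sessions is a plausible result of grade 3+ GU or GI toxicity, so selecting on completed treatment can amount to selecting on the outcome. A patient who has the event and stops because of it would leave both numerator and denominator, and accrual up to 100 per-protocol patients would put someone else in the place.

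The stake is the claim that the treatment is safe, on which the planned phase III trial depends. The design has little room for such a bias, because its type I error is already 4.6 % against a limit of 5 %.

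**Working it through.** **1. Reproducing the stated design.** Inputs from the sample size section: 50 patients at the interim, stop at 10 or more; 100 at the end, declare safety at 13 or fewer; null rate 20 %, alternative 10 %. With true rate p,

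P(declare safe) = Σ over x = 0…9 of P[Bin(50, p) = x] × P[Bin(50, p) ≤ 13 − x].

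- p = 0.10: 0.8716, which matches the stated 87.2 %.
- p = 0.20: 0.0459, which is below 0.05 as stated.

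The design is therefore correct if the rate in the analysed patients is the rate in the treated patients.

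**2. Recruitment against the per-protocol number.** The feasibility criterion accepts up to 5 % of patients without protocol radiotherapy. If 100 are recruited and 95 % adhere, 95 are per protocol. Reaching 100 would take 100/0.95 ≈ 105.3, that is 106 recruits. On the adherence reading, the feasibility criterion, the recruitment figure and the final denominator do not fit together.

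**3. Rate seen in a per-protocol set.** Let d be the share of all treated patients who have a grade 3+ event and are excluded, with no other patient excluded. The article gives no such figure, so d is an assumption. At a true rate of 20 %, the per-protocol rate is q = (0.20 − d)/(1 − d), and the share of toxic patients excluded is f = d/0.20.

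- d = 1 %: f = 5 %, q = 0.19/0.99 = 19.2 %
- d = 3 %: f = 15 %, q = 0.17/0.97 = 17.5 %
- d = 5 %: f = 25 %, q = 0.15/0.95 = 15.8 %

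**4. Chance of wrongly declaring safety at a true 20 %.** The article does not describe the interim 50 as per protocol, so both readings are shown.

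*Reading A: interim on the first 50 treated, final on 100 per protocol.* X ~ Bin(50, 0.20) and the trial continues if X ≤ 9. Of these X toxic patients, E ~ Bin(X, f) are excluded. A further 50 + E per-protocol patients are added, with Y ~ Bin(50 + E, q) events. Safety is declared if X − E + Y ≤ 13.

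*Reading B: both stages per protocol.* The formula in step 1 with p = q.

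| d (assumed) | Reading A | Reading B |
|---|---|---|
| 0 % | 4.6 % | 4.6 % |
| 1 % | 6.6 % | 6.8 % |
| 3 % | 12.5 % | 14.1 % |
| 5 % | 20.8 % | 26.7 % |

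**5. When there is no inflation.** Let a share g of non-toxic patients be excluded as well. Then q = 0.20(1 − f)/[0.20(1 − f) + 0.80(1 − g)].

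- f = g = 5 %: q = 0.19/(0.19 + 0.76) = 20.0 %, with no inflation (4.6 % in Reading B).
- f = 0, g = 5 %: q = 0.20/(0.20 + 0.76) = 20.8 %, and the error falls to 3.0 %.

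**6. At the decision boundary.** A result of 13/100 per protocol passes. If five further treated patients had a grade 3+ event and were left out, the rate among all treated is 18/105 = 17.1 %.

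**The case against.** The strongest reply is that the exclusion is inferred. The phrase appears once, undefined, in a sentence about continuing accrual, and could simply mean patients treated within this study. That sense agrees with a recruitment total of 100 and with a null hypothesis and interim rule that speak only of patients. The text is a condensed article, and the full protocol may define its analysis sets. The mechanism is also limited. Suboptimal hyperthermia sessions still count, omitted ones may be made up until the last fraction, and three of ten may be missed within the feasibility limit. Toxicity that appears after completed treatment stays in the count.

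This stands as a limit on how firmly the point can be put. It does not remove it. The article does state a population for the decision, uses protocol conformity elsewhere to mean adherence, and the two senses give different error rates.

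Two stronger readings are tempting, and the article does not support them:

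- **Feasibility is met by construction.** That would follow only if the feasibility rate were computed on the same per-protocol 100. The endpoint definition says only patients, and a 95 % threshold supposes that some of those counted do not adhere.
- **The error reaches 78 %.** That needs d = 10 %, half of all toxic patients excluded, and a per-protocol interim. If the interim counts all treated patients, the chance of passing it at a true 20 % is 44.4 %, so 78 % cannot occur. The figure for d = 10 % is then 40.6 %.

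**Conclusion.** The point holds as a conditional one. The final safety denominator is fixed with an undefined term whose adherence reading can leave out the harmed patients and conflicts with the recruitment total. On that reading, the stated significance level is exceeded once as few as 1 % of treated patients are excluded with a grade 3+ event (6.6 % or 6.8 %). At 5 % excluded it is about 21 % or 27 %.

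These figures assume a true rate of 20 %, that only toxic patients are excluded, and that the final set is filled up to 100. The excluded shares are assumptions. A reader might infer that the trial does drop and replace patients who stop for toxicity, or that its type I error is above 5 % as it stands. The article says neither, and with equal exclusion of toxic and non-toxic patients there is no inflation.

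**What to change.** Replace the per-protocol wording in the sample size section with a statement to this effect: the interim safety decision uses the first 50, and the final safety decision the first 100, patients who received at least one radiotherapy fraction or hyperthermia session. Patients who stop or deviate remain counted and are not replaced. The feasibility rate uses the same set of all treated patients. If a per-protocol set is kept, define it and use it only for a sensitivity analysis.

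This keeps the stated operating characteristics (type I error 4.6 %, power 87.2 %) and removes the conflict between 100 recruited and 100 per protocol. The cost is about one sentence of protocol text. Fewer than 100 patients may have full treatment, and the observed rates may look slightly less favourable.

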### Ethical and legal considerations

This study will be conducted in accordance with the guidelines of the local ethics committees. The protocol, patient information and informed consent sheets were submitted to the independent Ethics Committee of the Medical Faculty, University of Berlin, Germany and are submitted to the Ethics Committee of the Medical Faculty, University of Tuebingen, Germany. The “Independent Expert Committee of the DEGRO” stated that the dose range of 64–70 Gy as an application of therapeutic radiotherapy is within the frame of current health care. The study is in line with the Declaration of Helsinki, the laws and regulations of the country and in accordance with good clinical practice (ICH Harmonized Tripartite Guideline for Good Clinical Practice, http://www.ich.org/products/guidelines/efficacy/efficacy-single/article/good-clinicalpractice.html).

## Results and discussion

This study will investigate the safety and feasibility of moderately dose-escalated radiotherapy combined with regional hyperthermia for patients with biochemical recurrence after prostatectomy. The applied radiation technique, including IMRT or rotational techniques, and thermometry (MR-based thermometry is allowed) of hyperthermia both represent the latest technical developments [37]. This ensures that the study is performed at the highest technical level and is essential to minimize potential modality-related side-effects, since knowledge on radio-thermotherapy after prostatectomy is limited [23].

All treatment optimization studies on sRT share the same local risks. Treatment is given to the urethral anastomosis where fibrosis, stenosis or, in the worst case, a leakage could occur. With regard to the most technically advanced randomized trial on postoperative radiotherapy using 3D-conformal radiotherapy (3D-CRT) to the prostatic fossa, the total dose of 60 Gy was associated with only 0.3 % G3+ side effects (1/307) [38]. Goldin et al. ascertained that there was no difference in toxicity between IMRT and 3D-CRT in the postoperative setting [39]. It might be speculated that this finding was based on the general low frequency of side effects in this radiation dose range and was independent of the radiation technique. At higher radiation dose levels, IMRT was beneficial for patients with definitive prostate radiotherapy. This was demonstrated in a propensity score-adjusted analyses (*n* = 12,976) of data from the Surveillance, Epidemiology, and End Results (SEER) database [40]. The use of IMRT compared with 3D-CRT was associated with less gastrointestinal morbidity and fewer hip fractures, but more erectile dysfunction potentially caused by the higher total dose in the IMRT group. The RTOG target volume definition [41] used in the Godin study was clearly larger compared to the EORTC target volume definition. The larger and more regular the treatment volume, the smaller the benefit from IMRT. Consequently, findings from trials using another target volume definition can only be applied with caution.

The SAKK 09/10-study did not detect significant differences in CTCAE-measured acute toxicity between 64 Gy and 70 Gy. Urinary quality of life was slightly but significantly worsened in the higher dose group, independent of radiation treatment technique [12]. Reduction of the high-dose target volume in cases of clear identification of high risk areas (modified boost concept) was reasonable and was therefore introduced in this study. A first hint on efficacy of radio-thermotherapy (secondary endpoint) could allow comparison of this study with the SAKK 09/10 outcome data, since target definition, cancer-related inclusion and exclusion criteria were equal. A recently published retrospective study demonstrated a significant benefit for patients with positive margin but no macroscopic recurrence treated to at least 70 Gy compared to a patient cohort with a total dose of 66 Gy (100 % vs. 66.7 %) [42].

The RTOG 96–01 study demonstrated that sRT to 64.8 Gy and 2 years of ADT increased PSA-control (57 % vs. 40 %) without any influence on overall or disease-specific survival at 7 years [11]. However, long-term ADT is associated with general side effects such as sarcopenia, erectile dysfunction, fatigue and osteoporosis with a risk of fractures [43]. Furthermore, there are hints that changes in lipid metabolism could lead to a greater incidence of diabetes and cardiovascular disease, including renal complications [44–46]. Consequently, Ahmadi et al. concluded that the best way of preventing side effects is to only use ADT when it is absolutely indicated [43]. Cardiovascular mortality did not differ in otherwise healthy study participants of 8 randomized trials on long-term ADT [47]. However, the influence of long-term-ADT in patients with pre-existing co-morbidities remains unclear. Therefore, hyperthermia could become a sRT optimization tool to circumvent long-term ADT and its suspected side-effects.

## Conclusion

The ongoing phase II study implements highly precise image-guided radiotherapy and regional hyperthermia. If the phase II study is found to be safe and feasible, a multicenter phase III study is planned to test whether the addition of ten hyperthermia applications to dose-intensified sRT improves biochemical control.
